## Abstract

**Background:**

The third most frequent chronic condition, and the fourth most common cause of death, in Poland is chronic obstructive pulmonary disease (COPD). The diagnosis and treatment of COPD is the responsibility of the general practitioner (GP); the GP also serves as gatekeeper, referring patients to the other levels of public health care system when necessary. Undertreatment of COPD can result in a greater frequency of exacerbations and hospitalizations. Elderly patients require special attention due to the increased prevalence of COPD and systemic comorbidities. However, both the occurrence of exacerbations and the quality of life of the patients may be improved by developing and implementing guidelines for practice and ensuring their adherence. This proposal concerns the development of a checklist-based educational program to assist general practitioners in managing COPD patients.

**Methods:**

No less than eighty-four general clinics in the Lodz region, Poland (28 clusters in each of three study arms), will be identified, randomized, and included in the trial. The trial will be based on anonymized data in electronic health records within the national public health care system.

The educational intervention program will consist of GPs in two intervention arms being provided with a COPD management checklist: those in the first intervention arm with receive the checklist once at the beginning, while those in the second with receive it twice. The third (control) arm receives standard care without the checklist.

The study used the International Code of Diseases (ICD)-10 for COPD. The primary aim is to determine the effect of interventions delivered to general practitioners (GPs) in primary health care. These interventions are aimed at decreasing the hospitalization of elderly patients with medical code J-44 (COPD) as the main reason for hospital admission.

**Discussion:**

The results of this trial will be directly applicable to primary care in Poland and add new data to the growing body of evidence regarding interventions aimed at improving chronic illness care.

**Trial registration:**

This trial has been registered with the Clinical Trials Protocol Registration System. Please see in ClinicalTrial.gov identifier (NCT Number): NCT04301505. Registered on 10 March 2020.

**Supplementary Information:**

The online version contains supplementary material available at 10.1186/s13063-021-05103-0.

## Contribution to the literature

This document describes the design and implementation of a pragmatic study to assess the effectiveness and implementation of a strategy based on a structured checklist in primary care.The impact of the checklist on care in COPD will be determined using Big Data methods.The clinical effectiveness of repetition of COPD checklist exposure in primary care will be assessed.

## Introduction

### Background

Caring for patients with chronic obstructive pulmonary disease (COPD) presents a substantial challenge for general practitioners (GPs). COPD is a non-reversible lung condition characterized by shortness of breath, chronic cough with sputum production, emphysema, and systemic pulmonary inflammation.

Although data on its prevalence in the general population is limited, the true prevalence of COPD among the Danish population is believed to be 9% (95% CI 8–10%), with the highest prevalence observed among current smokers (23%) and former smokers (17%) as well as among seniors (total = 18%; men = 21%; women = 15%) [1].

In Australia, approximately 5% of patients in general practice were found to suffer from COPD; this number rises to approximately 10% among patients aged 65 years or above [2].

Although the scope of the problem is recognized in Poland, relatively little concrete research data exists, especially concerning elderly patients in primary care. It is estimated that the prevalence of COPD is approximately two million out of a population of about 38 million; this places COPD as the third most widespread chronic condition in the country and the fourth most common cause of death [3].

However, international studies indicate that the prevalence of COPD in Poland may be considerably higher than previously anticipated (10% of the examined population) [4].

In Poland, almost everyone registered with the national public health care system (NFZ) is also registered with a GP. The GP acts as gatekeeper, referring patients with diagnostic or treatment problems to the other levels of the public health care system. However, it is possible that some mistakes may occur with diagnosis and treatment. Under-treatment can result in unnecessary symptom burden, impaired COPD control, and more frequent exacerbations and hospitalization, while over-treatment may lead to increased healthcare costs and potential iatrogenic effects [5].

Elderly patients are at greatest risk of developing COPD and its components: emphysema, chronic bronchitis, and bronchiectasis. Bacterial and viral infections also play a role in acute exacerbations of COPD, and elderly patients are at greater risk of infection by antibiotic-resistant bacteria [6].

To introduce effective interventions and inform efforts for health resource allocation, it is necessary to understand the features of COPD in older patients. Non-smoking seniors tend to demonstrate a greater prevalence of COPD and a higher rate of systemic comorbidities. In addition, acute exacerbations in older patients tend to have a poorer outcome, reflected in an increased rate of hospitalization, longer stays, and increased re-hospitalization and mortality rates. Seniors are also more likely to experience impaired cognitive functions and problems affecting the hand joints, thus impairing the effectiveness of inhaled medications and the outcome of care. Even for those who are competent at using inhalers, the evidence for their efficacy in older patients is uncertain [7].

A Danish study indicates substantial room for improvement in GP clinics [8].

Other studies indicate that even the routine implementation of community health assessment and improved planning measures can lead to improved health outcomes [9]. The annual healthcare costs for primary care for these patients are estimated to be approximately 53.6 million euros. Various interventional approaches have been used [10].

COPD exacerbations significantly impact health-related quality of life and disease progression, and healthcare costs associated with severe exacerbation-related hospitalization range from $7000 to $39,200 in the USA. However, the timely and appropriate application of maintenance pharmacotherapy, particularly dual bronchodilators for maximizing bronchodilation, can significantly reduce exacerbations, and multidisciplinary disease-management programs including pulmonary rehabilitation, follow-up appointments, aftercare, inhaler training, and patient education can reduce hospitalizations and readmissions for patients with COPD [11].

However, few physicians are aware of practice guidelines and continuing medical education (CME) programs [12]. Current guidelines are still poorly adhered to by GPs, and generally, little is known of the role of specific non-clinical interventions in facilitating GP care for COPD patients. To remedy this, the EU-funded TICD project, a cluster randomized controlled trial (RCT), was performed to identify possible determinants of COPD care and tailored interventions to facilitate better implementation in general practice [13]. Such intervention appears feasible [14].

The present study will identify the most effective method for delivering an educational intervention to general practitioners based on a simple consensus process.

This protocol has been written in line with the SPIRIT standard [15].

### Objectives

To determine the effect of intervention aimed at decreasing the hospitalization of elderly patients with J-44 as the main reason for hospital admission, compared to those receiving usual careTo optimize the management of elderly COPD patientsTo examine whether intervention 1 and intervention 2 are effective, pragmatic, and feasible within the primary care setting

### Trial design

The trial is planned as a 1-year, three-arm, pragmatic, cluster randomized trial (CRCT). It will compare the effectiveness of interventions in two arms (single intervention and double intervention) at reducing the hospitalization of seniors in primary care with the J-44 code as a main reason for admission, compared to those experiencing usual care.

## Methods/design

### Study setting

Eighty-four GP clinics in the Lodz voivodship in Poland will be identified at baseline using data from the National Health Fund’s (*Narodowy Fundusz Zdrowia*, NFZ) electronic medical records (EHR). They will be randomly selected using the following criteria: clinics with at least 30 patients per clinic, aged 65 years and older with COPD. Patients with COPD will be identified by the ICD-10 code J-44 in NFZ electronic medical records; exacerbations will be defined as cases hospitalized with the J-44 code as the main reason for admission.

### Observation period

The study will include data for 1 year, from March 2020 until February 2021. Data extraction and analysis will take place from March until June 2021 (see Fig. 1).

**Fig. 1 Fig1:**
[figure not shown]
The schedule of the study

The endline data for the clinic and patients will be collected after 1 year. We will consider additional data collections from other time points based on the development of the COVID situation.

### Sample size

A minimum number of 84 GP clinics with at least 30 J-44 patients per clinic is required to provide a sufficient sample size for a three-arm cluster randomized controlled trial: 84 clusters and at least 2520 subjects are needed (28 clusters in each study arm) to detect a difference of 0.026 between mean event rates of hospitalization with ICD-10 code J-44 as the main reason for admission. This assumes a 25% reduction in total number of events after the intervention in the first arm (receiving checklist once) and 50% reduction in total number of events after the interventions in the second arm (receiving checklist twice) compared to the control group not receiving any intervention (standard care). It is also assumed the tests will have 80% power, a two-tailed alpha of 0.05, and intra-cluster correlation of 0.01.

Data collected from electronic health records in 2016 indicate that the mean event rate of “hospitalized with ICD-10 code J-44 as the main reason for admission” in the control group is 0.105, and the standard deviation is 0.306. The unadjusted sample size was calculated for differences between three means for one-way ANOVA.

To compare the individuals hospitalized with the J-44 code in the three arms after 1 year, the difference between the mean event rates of the three groups was calculated according to Donner and Klar [16].

A standard sample size formula was used to calculate the initial unadjusted sample size requirements, followed by appropriate adjustment for clustering by general practice according to Campbell et al. [17], with expected small clustering effect (ICC = 0.01) [18, 19].

To prevent loss to follow-up among practices/participants, an enlarged overall sample size will be deemed appropriate to ensure adequate power.

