### Outcomes

*The primary outcome of the study* will be the effect of the interventions on the proportion of “hospitalization with the J-44 code as a main reason for admission,” and the proportion of deaths of elderly COPD patients, registered within practices after 1 year.

*Primary outcome at the patient level* will be assessed as the proportion of cases between the three arms (intervention 1, intervention 2 and control) at the end of the 1-year study period. Proportion of cases (event rates) of binary variables of exacerbation outcome will be assessed based on “hospitalization with the J-44 code as a main reason for admission,” and the proportion of deaths of elderly COPD patients.

The effect of the educational intervention will be evaluated using logistic 2-level regression analysis, based on odds ratios (OR) and 95% confidence limits.

We will examine the association between intervention and COPD exacerbation, using a case-control approach. Cases will be selected among COPD exacerbation after 1 year. Control subjects will be selected among COPD patients.

*Secondary outcome at the patient level* will be the proportion of the control and intervention arms regarding the specific short- and long-acting drugs prescribed after 1 year.

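### The claimed 80% power for a 0.026 difference belongs to the three-arm omnibus test; the 0.026 contrasts themselves have about 34% to 48% power

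*Protocol article*

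**What the plan says.** The protocol article's Sample size section states: "A minimum number of 84 GP clinics with at least 30 J-44 patients per clinic is required". It gives the purpose as "to detect a difference of 0.026 between mean event rates of hospitalization with ICD-10 code J-44 as the main reason for admission", with 28 clinics per arm, 80% power, two-tailed alpha 0.05 and ICC 0.01. The control rate is 0.105 with SD 0.306. The assumed effects are a 25% reduction with one checklist and a "50% reduction in total number of events after the interventions in the second arm (receiving checklist twice) compared to the control group". The section also discloses the method: "The unadjusted sample size was calculated for differences between three means for one-way ANOVA", followed by an adjustment for clustering.

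The planned analysis is different. Under Outcomes, the effect is to be evaluated by two-level logistic regression, "based on odds ratios (OR) and 95% confidence limits". Trial design and Objectives set each intervention against usual care and ask whether both work. The end of the Background says that the study will "identify the most effective method for delivering an educational intervention", and the Contribution to the literature section promises to assess the effect of repeating the checklist.

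**The concern.** Under the protocol's own assumptions, 0.026 is the step between adjacent arms: control to single checklist, and single to double. The largest gap, control to double, is twice that. A three-group F test draws most of its power from the largest gap, and a significant result does not establish any particular 0.026 difference. Attaching the F test's 80% to a difference of 0.026 therefore describes a test that was not sized.

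The two comparisons with a 0.026 gap answer stated aims: whether one mailing works, and whether a second adds anything. If they have well under 80% power, a non-significant result says little. A reader relying on the Sample size section would still take it as strong evidence of no effect. The Discussion links an effective result to wide-scale application, so a wrong reading of either comparison could influence what is rolled out.

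**Working it through.** **Inputs (all from Sample size).** Control rate 0.105; SD 0.306; reductions of 25% and 50%; 28 clinics of 30 per arm, so 840 patients per arm; ICC 0.01; two-sided alpha 0.05.

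**Rates and gaps.**
- Single checklist: 0.105 × 0.75 = 0.07875. Double checklist: 0.105 × 0.50 = 0.0525.
- Control − single = 0.02625; single − double = 0.02625; control − double = 0.0525.

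**Reproducing the plan's figure (omnibus F test).**
- SD of the three rates = √(0.001378/3) = 0.02143, so Cohen's f = 0.02143/0.306 = 0.0700.
- Noncentral F with three groups, alpha 0.05 and 80% power: 656 per arm before clustering.
- Design effect = 1 + 29 × 0.01 = 1.29, and 656 × 1.29 = 846 per arm.
- 846/30 = 28.2 clinics, against the stated 28.
- At 840 per arm, effective n = 840/1.29 = 651. The noncentrality is 651.2 × 0.001378/0.306² = 9.58, and power is 79.7%.

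The stated size is therefore the omnibus test.

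**Power of each pairwise contrast at the same size.**
- Constant SD: SE = 0.306 × √(2/651.2) = 0.01696. For a gap of exactly 0.026, z = 0.026/0.01696 = 1.53 and power is 33%. For 0.02625, z = 1.55 and power is 34%. For 0.0525, z = 3.10 and power is 87%.
- Binomial variances: SE = √[(p₁(1−p₁) + p₂(1−p₂))/651.2]. This is 0.01599 (control, single), 0.01370 (single, double) and 0.01486 (control, double), so z = 1.64, 1.92 and 3.53.

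| Contrast | Gap | Power, SD 0.306 | Power, binomial variance |
|---|---|---|---|
| Single vs control | 0.02625 | 34% | 38% |
| Double vs single | 0.02625 | 34% | 48% |
| Double vs control | 0.0525 | 87% | 94% |

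A cluster-level beta-binomial simulation (20,000 runs, ICC 0.01) agrees with the binomial column: 36%, 47% and 94%.

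**Could another convention rescue 80% for 0.026?**
- No clustering at all: 41% to 58%.
- One-sided test: 46% to 61%.
- Alpha split to 0.025: 24% to 37%.
- Omnibus test with 0.026 as the largest gap among the arms: about 87 to 115 clinics per arm.

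**What the design can detect, and what 0.026 would need.**
- Smallest pairwise difference with 80% power at SD 0.306: (1.96 + 0.84) × 0.01696 = 0.048, a relative reduction of 0.048/0.105 = 45%.
- 80% power for exactly 0.026 at SD 0.306: 2 × (1.96 + 0.84)² × 0.306²/0.026² gives 2175, and 2175 × 1.29 ≈ 2806 patients, or 94 clinics of 30 per arm.
- Single vs control with binomial variance and 0.02625: 1900 × 1.29 = 2451 patients, or 82 clinics.
- Double vs single: 61 to 62 clinics with binomial variance, 92 to 94 with SD 0.306.

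**The case against.** *The ANOVA and both reductions are disclosed.* This is true, and the ANOVA arithmetic is sound. The fault lies in attaching its power to a difference of 0.026. Disclosure lets a careful reader discover the mismatch but does not make the sentence correct.

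*Thirty per clinic is a minimum, so these powers are floors.* This stands as a qualification. Eligible clinics have 30 or more such patients, at least 84 clinics are planned, and an enlarged sample is foreseen without a figure. No average clinic size is given, so a range is needed. With 28 clinics per arm and ICC 0.01, single versus control has 46% to 51% power at 50 patients per clinic and 62% to 68% at 100; 80% needs roughly 200 to 320. Double versus single reaches 80% at 100 per clinic, but only with binomial variances (62% at SD 0.306). The claim is tied to 84 clinics and 2520 patients, where it fails.

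*The variance assumption matters.* This also stands. With binomial variances the omnibus test has about 89% to 91% power, so its 80% figure belongs to the constant SD of 0.306. For double versus single, where both arms have rates below control, the binomial 48% is the more relevant figure.

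*The article names no reference arm, so a joint test of arm is possible.* It is, and contrast details may sit in a plan not shown. But the Objectives and Trial design sections frame the question as each intervention against usual care, and a joint test would still not give 80% power for a 0.026 difference.

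*Confidence limits are already planned.* They will show the imprecision, but do not correct the stated power.

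**Conclusion.** The concern holds. The sample size reproduces as an omnibus three-arm test (79.7% power), and the text wrongly presents that power as applying to a 0.026 difference. At the stated size, single versus control has 34% to 38% power, double versus single 34% to 48%, and double versus control 87% to 94%. These figures rest on the protocol's rates, SD and ICC, on 30 patients per clinic and on two-sided 0.05 without multiplicity adjustment. Larger clinics would raise them; splitting alpha would lower them. No convention tried gives 80% for 0.026 at 28 clinics of 30 per arm.

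**What to change.** Replace the power statement in Sample size with wording along these lines:

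> With 84 clinics at the minimum of 30 patients each, ICC 0.01 and two-sided alpha 0.05, the omnibus three-arm test has about 80% power under reductions of 25% and 50% (SD 0.306; about 89% to 91% with binomial variances). Power is about 87% to 94% for double checklist versus control, 34% to 38% for single checklist versus control and 34% to 48% for double versus single.

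Delete the claim of 80% power for 0.026. Name double checklist versus control as the adequately powered contrast, and state that the other two will be read from their confidence intervals, with non-significance not taken as evidence of no effect. If the average clinic size is known from the health fund's records, add power at that size.

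The cost is a less favourable power statement and a commitment on interpretation, best fixed before the outcome data are analysed. It needs no extra clinics or change to allocation or data collection, so it remains feasible with the trial already in its intervention phase.

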#### Test statistics for primary outcome and dependent variable

The effect of the educational interventions will be evaluated using two-level logistic regression models with a dependent binary variable (case-control, cross-sectional analysis), with patients nested within practices.

Data regarding hospitalization will be collected directly from patient electronic health records held by the National Health Fund (NHF—the state health insurance system). Patients registering exacerbation, defined as “hospitalization of patients with the J-44 as a main reason for admission,” will be classed as cases. Control subjects will be collected from electronic health records held by the NHF, defined as COPD (J-44), age over 65, with low treatment cost, and no constantly reimbursed drugs. Data will be collected after the 1-year study period (cross-sectional) within the Lodz voivodeship.

Descriptive statistics and logistic regression will be employed. The level of statistical significance will be *p* < 0.05.

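### The 80% power and 84 clinics come from a three-mean ANOVA with the control-arm SD in every arm; with binomial variances a joint three-arm test has about 88-90% power, while the odds-ratio contrasts have about 37%, 48% and 93%

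*Protocol article*

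**What the plan says.** The Sample size section of the protocol article takes its inputs from 2016 health records: "the mean event rate of “hospitalized with ICD-10 code J-44 as the main reason for admission” in the control group is 0.105, and the standard"; the SD given there is 0.306. It assumes a 25% reduction in events with one checklist and a 50% reduction with two, and aims at a difference of 0.026 between mean event rates. The method is given as follows: "The unadjusted sample size was calculated for differences between three means for one-way ANOVA", with a later adjustment for clustering. The error rates and clustering are also stated: "It is also assumed the tests will have 80% power, a two-tailed alpha of 0.05, and intra-cluster correlation of 0.01". The result is that "A minimum number of 84 GP clinics with at least 30 J-44 patients per clinic is required", that is 28 clinics per arm and at least 2520 patients. On loss, the section adds: "To prevent loss to follow-up among practices/participants, an enlarged overall sample size will be deemed appropriate to ensure adequate power". It gives no loss figure.

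The analysis is described elsewhere. Under the heading Test statistics for primary outcome and dependent variable, the article states: "The effect of the educational interventions will be evaluated using two-level logistic regression models with a dependent binary variable". The Outcomes section says the effect is read from odds ratios with 95% confidence limits. Neither section names a joint test of the three arms.

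**The concern.** The outcome is whether or not a patient was hospitalized, so its SD is not a free input. The value 0.306 is the binomial SD at the control rate. Carrying it into the two intervention arms contradicts the lower rates that the same section assumes there. The statistic used for sizing (an F test on three means with one common variance) is also not the one planned for analysis (a logistic model, whose variance follows each arm's rate).

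A reader who sees 80% power and a stated difference of 0.026 will take it that each comparison of interest has about a one-in-five chance of being missed. If the true power differs by comparison, the published figure misinforms in both directions: too low for a joint test, and far too high for the contrast of one checklist against usual care.

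**Working it through.** **Inputs, all from Sample size.** Control rate 0.105. One checklist: 0.105 × 0.75 = 0.07875. Two checklists: 0.105 × 0.50 = 0.0525. The step between adjacent arms is 0.02625, the stated 0.026. There are 28 clinics of 30 patients per arm, so 840 patients. With ICC 0.01 the design effect is 1 + 29 × 0.01 = 1.29, and the effective n is 840 / 1.29 = 651 per arm. Two-sided alpha is 0.05.

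**Reproducing the plan's figure.** The sum of squared deviations of the three rates from their mean is 2 × 0.02625² = 0.001378. With SD 0.306 in every arm:

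- Noncentrality λ = 651 × 0.001378 / 0.306² = 9.58, and the noncentral F (2 df) gives power 79.7%.
- Solving for 80% gives 656 per arm unadjusted; × 1.29 = 846; / 30 = 28.2 clinics per arm, or about 2539 patients against the 2520 printed.

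So the printed sizing is this ANOVA with the control SD used throughout.

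**SDs implied by the assumed rates, √(p(1−p)).**

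| Arm | Rate | p(1−p) | SD |
|---|---|---|---|
| Control | 0.105 | 0.0940 | 0.307 |
| One checklist | 0.07875 | 0.0725 | 0.269 |
| Two checklists | 0.0525 | 0.0497 | 0.223 |

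The mean variance is 0.0721, against 0.306² = 0.0936 in the plan's calculation.

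**Joint 2-df test at 28 clinics per arm.**

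- Mean binomial variance: λ = 651 × 0.001378 / 0.0721 = 12.4, power 89.4% (noncentral F), or 88.3% with 81 cluster degrees of freedom.
- Wald test on the logit scale: λ = 12.0, power 88.4%.
- Pearson: 89.3%. Likelihood ratio: 89.8%.
- Simulated random-intercept logistic model with a likelihood-ratio test: 90.2% with beta-binomial clusters (1500 runs, false-positive rate 5.1%), and about 92% with logit-normal clusters (600 runs, false-positive rate about 5.7%).

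By formula, this joint test reaches 80% at about 22-23 clinics per arm.

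**Pairwise odds ratios (Wald on the log odds ratio).** SE = √(1/(651·p₁(1−p₁)) + 1/(651·p₂(1−p₂))), and power = Φ(|log OR|/SE − 1.96).

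| Contrast | OR | \|log OR\| | SE | Power at 28 per arm | Clinics per arm for 80% |
|---|---|---|---|---|---|
| One checklist v control | 0.729 | 0.317 | 0.194 | 37% | 82-83 |
| Two checklists v control | 0.472 | 0.750 | 0.217 | 93% | 18-19 |
| One v two checklists | 0.648 | 0.434 | 0.228 | 48% | 61 |

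The lower end of each range in the last column comes from the comparison of two proportions, which gives powers of 37%, 94% and 48%. No adjustment for multiple comparisons is applied. At 22-23 clinics per arm the first contrast would have about 31-32% power.

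**The case against.** The strongest defence is that nothing has been miscalculated. The section states its method openly, and the figures reproduce under it. The control SD is the largest of the three, so using it everywhere is cautious for a joint test, and 84 is described as a minimum. That stands. The issue is a mismatch of variance and test rather than a slip of arithmetic, and for a joint test the mismatch errs on the safe side. It is not safe for the single-checklist contrast, and caution does not make 80% the right figure for any of the comparisons above.

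A reader might also infer that the planned logistic analysis has 88-90% power, that about 69 clinics (3 × 23) would therefore do, and that the margin up to 84 can serve as the allowance for lost practices. The documents do not support this. The 88-90% belongs to a joint 2-df test that the article nowhere names. What it does name is odds ratios with confidence limits, and its objectives ask whether each of the two interventions is effective. For the stated difference of 0.026, the direction reverses: 28 clinics per arm are too few for 80%, not too many.

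A further fair point is that the figures here are conditional. They take exactly 30 patients per clinic where the plan says at least 30. They analyse the whole cohort, although Outcomes and the test-statistics section also describe selecting cases and controls. They cover hospitalization only, although deaths also appear in the primary outcome. None of this was modelled.

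**Conclusion.** The point holds in a limited form. The printed 80% and 84 clinics rest on a common SD that the plan's own assumed rates rule out in two of three arms, and on a test that is not the planned one. With binomial variance in each arm, a joint three-arm test has about 88-90% power, some 8-10 points above the printed figure. The odds-ratio contrasts have about 37%, 93% and 48%. The conclusion is therefore neither that the trial is too large nor that it is uniformly too small: it depends on a test that the text does not specify.

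This rests on 28 clinics of exactly 30 patients per arm, ICC 0.01 on the proportion scale, two-sided alpha 0.05 without multiplicity adjustment, no loss, and analysis of all COPD patients in the clinics.

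**What to change.** In Sample size:

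- Replace the common SD of 0.306 with p(1−p) at each arm's assumed rate, keeping the design effect of 1.29.
- Name the test to which the power refers.
- State that 28 clinics of 30 per arm give about 88-90% power for a joint three-arm test, and print beside it about 37% for single checklist versus control, 93% for double versus control and 48% for single versus double.
- Keep 84 clinics as a minimum and keep the planned enlargement for loss. Do not write that about 69 clinics suffice or that the margin above 69 is the loss allowance.

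The cost is a correction of text and numbers, with no change to clinics, data or analysis. The price is candour: the single-checklist contrast will be shown as much weaker than the printed 80%, and so will single versus double.
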